#### Secondary Outcomes

The secondary outcomes will be (1) changes in physiological parameters (such as heart rate and pulse oximetry) during and after the intervention compared with baseline, (2) occurrence of side effects, (3) deviation from the normal procedure length, (4) rescheduling of procedures in the event cooperation is impossible, and (5) salivary amylase levels.

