**Methods:**

This pilot randomized controlled trial study will follow a parallel design including 2 groups: a control group (clinic’s standard care using a wall TV) and an experimental group (using a VR game). We will randomize 20 participants to either group. Recruitment will be carried out at the dental clinic of the Centre Hospitalier Universitaire Sainte-Justine, a tertiary-quaternary care center that mostly serves pediatric patients with SHCN. The primary outcome will be patient recruitment rates and completion rates of planned procedures. DFA in children will be assessed using both an observation-based proxy assessment with the Venham Anxiety and Behavior Rating Scale and physiological assessments using parameters such as change in heart rate and levels of salivary alpha-amylase as a stress biomarker before and 10 minutes after the procedure. Sociodemographic characteristics, measures of the levels of parent and health care professional satisfaction, occurrence of side effects, and any deviation from normal procedure length will also be collected. Descriptive statistics, nonparametric tests, and effect sizes will be used for demographic and clinical variables and to present parent and health care professional satisfaction levels as well as procedural time.

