### Objectives

The primary research objectives are to determine (1) the feasibility and acceptability of VR distraction for children with special needs requiring dental procedures, (2) compare parent and health care professional satisfaction levels between the VR distraction group and the clinic’s standard mounted TV showing cartoons, and (3) observe the preliminary effects of VR distraction on reducing patient anxiety during dental procedures compared with standard nonpharmacological behavior management.

The secondary objectives of this study are to compare the following between the VR distraction group and the clinic’s standard mounted TV showing cartoons: (1) physiological parameters (pulse and oxygen saturation), (2) the occurrence of side effects, (3) dental procedure length, (4) the number of retakes of dental procedures due to DFA, and (5) salivary amylase levels.

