### Sample and Setting

This pilot will include 20 participants, totalling 10% of the expected 200 children to be included in the final study. All participants in this pilot study will be allocated in an equal ratio of 10 per group. Recruitment will be carried out at the dental clinic of the Centre Hospitalier Universitaire Sainte-Justine, a pediatric hospital in Montreal, Canada. This clinic mostly serves patients with SHCN such as craniofacial abnormalities, autism spectrum disorder, cancer, and others. Pediatric patients with SHCN represent around 80% of the total clientele of this clinic, while the rest is comprised of otherwise healthy patients with dental traumas and other dental emergencies.

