### Study Time Points

Sociodemographic data will be assessed before the intervention at baseline (T0) to establish a baseline using a simple questionnaire completed by the parent or legal guardian present while sitting in the waiting room. Salivary alpha-amylase samples will be collected at T0 and after the intervention/procedure (T2; Multimedia Appendix 1). Measures of specific dental procedure–related anxiety and uncooperative behavior will be assessed at T0, during the procedure (10 minutes from the start; T1), and immediately after the end of the procedure (T2). Physiological parameters will be measured at T0, during the intervention (T1), and T2. Data on occurrence of side effects will be assessed and monitored at all times for the duration of this study. All clinical monitoring will be performed by the dental resident on site. Measures of parent or legal guardian and health care professional satisfaction will be assessed at T2.

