### Statistical Analysis

Analysis will be conducted using the SAS (SAS Institute) statistical analysis software (version 9.4). Descriptive statistics, by treatment, will be conducted for demographic and clinical variables and will be used to present sociodemographic and clinical data, parent and health care professional satisfaction levels, and procedural time. Due to a small sample size, we will also assess effect sizes.

For the pilot project, we plan to perform descriptive analyses of the sample as well as comparative analyses between the 2 groups. Nonparametric tests for procedural type, age, parental presence, parental and health care satisfaction levels, and baseline (T0) anxiety score measurement will be used to assess the composite outcome for mean salivary cortisol level and mean difference in anxiety score (using the Venham Clinical Cooperation Scale and Venham Clinical Anxiety Scale) between the experimental and control groups at T2. Analyses will be carried out according to the intention-to-treat principle, with a significance level (α) of .025, considering Bonferroni's correction.

For secondary outcome analyses, nonparametric tests adjusted for procedural type, age, and parental presence will be used to assess the mean procedural length at T2 using the VAS and 6-item tailored questionnaire, respectively. Comparison of dichotomous variables including the necessity for procedural retakes, use of other nonpharmacological interventions, and the occurrence of side effects will be assessed using the Cochran-Mantel-Haenszel test.

The study data will be recorded in the REDCap system belonging to URCA. The data manager associated with URCA and independent of the study will be responsible for the storage of the recorded data. However, a URCA biostatistician independent of the study will be responsible for the data analysis. The data analysis plan will be discussed with the principal investigator ([name]). Interjudge correlations will be conducted for the video tape analysis. Two judges will independently rate the anxiety measure on the videotapes. Subsequently, we will conduct intraclass correlation coefficient analyses to compare the scores for each of the recruited patients between the 2 judges.

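### Heart rate and oxygen saturation are defined as change from T0, and no adjustment for the T0 value is listed; adding it would usually sharpen the 10 v 10 comparison

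*Protocol article*

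**What the plan says.** The protocol article, under Secondary Outcomes, defines the outcome as "changes in physiological parameters (such as heart rate and pulse oximetry) during and after the intervention compared with baseline". The abstract's Methods paragraph uses the same form when it lists the ways in which dental fear and anxiety will be assessed: "physiological assessments using parameters such as change in heart rate". The Objectives section makes pulse and oxygen saturation a comparison between the VR group and the wall-TV group. The T0 value is available, because under Study Time Points "Physiological parameters will be measured at T0, during the intervention (T1), and T2".

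The Statistical Analysis section names no test for heart rate or saturation. Its one covariate list for secondary outcomes reads "nonparametric tests adjusted for procedural type, age, and parental presence will be used to assess the mean procedural length at T2", so procedural length is the only outcome attached to that list. A baseline value appears once, in the anxiety and biomarker analysis: "baseline (T0) anxiety score measurement will be used to assess the composite outcome". No T0 physiological value is listed as an adjuster anywhere.

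On size, Sample and Setting says: "This pilot will include 20 participants, totalling 10% of the expected 200 children to be included in the final study". Allocation is 10 per group. Randomization and Allocation describes permuted blocks and names no stratification factor.

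**The concern.** Subtracting T0 fixes the slope of follow-up on baseline at 1. With similar spread at the two times, the actual slope is about the correlation between them, which is below 1. Raw change then over-corrects: a child whose T0 pulse is high by chance tends to show a fall whatever the treatment. Using T0 as a covariate estimates the slope from the data.

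Two things are at stake. One is precision, in a sample with little to spare. The other is the reading of the single estimate that this pilot will produce. With 10 children per arm, mean T0 pulse will often differ between arms, and an unadjusted change contrast passes part of that difference into the apparent effect of VR. The Statistical Analysis section says that effect sizes will be assessed because the sample is small, and the Conclusion says the results can serve as preliminary data, so the estimate will be looked at.

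**Working it through.** **The plan's own figures.** 0.10 × 200 = 20 children, and 20 / 2 = 10 per arm. These reproduce. The document states no power, effect size, SD or correlation for heart rate.

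**Assumptions.** Equal SD at T0 and follow-up (set to 1), normal data, and a T0-to-follow-up correlation rho between 0.3 and 0.9. None of these comes from the document.

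**Precision.** The variance of the between-arm difference is proportional to 2(1 − rho) for raw change and to 1 − rho² for the T0-adjusted analysis. The large-sample ratio is therefore 2(1 − rho) / (1 − rho²) = 2 / (1 + rho). Estimating the slope with N = 20 multiplies the adjusted variance by 1 + 1/(20 − 4) = 1.0625, so the ratio at 10 v 10 is 2 / [(1 + rho) × 1.0625]. The standard errors are sqrt(2(1 − rho) × 2/10) for change and sqrt((1 − rho²) × 1.0625 × 2/10) for the adjusted analysis. The simulated column comes from 40,000 trials of 10 v 10.

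| rho | 2(1 − rho) | 1 − rho² | Large-sample ratio | Ratio at 10 v 10 | Simulated ratio | SE change | SE adjusted |
|---|---|---|---|---|---|---|---|
| 0.3 | 1.40 | 0.91 | 1.538 | 1.448 | 1.460 | 0.529 | 0.440 |
| 0.5 | 1.00 | 0.75 | 1.333 | 1.255 | 1.260 | 0.447 | 0.399 |
| 0.6 | 0.80 | 0.64 | 1.250 | 1.176 | 1.183 | 0.400 | 0.369 |
| 0.7 | 0.60 | 0.51 | 1.176 | 1.107 | 1.113 | 0.346 | 0.329 |
| 0.8 | 0.40 | 0.36 | 1.111 | 1.046 | 1.044 | 0.283 | 0.277 |
| 0.9 | 0.20 | 0.19 | 1.053 | 0.991 | 0.993 | 0.200 | 0.201 |

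The two methods break even where 2 / (1 + rho) = 1.0625, that is at rho = 2/1.0625 − 1 = 0.88.

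**Power, for illustration only.** For a true effect of 1 SD at two-sided .05 with normal-theory tests, simulated power for change v adjusted is 43.5% v 57.7% (rho 0.3), 56.2% v 65.9% (0.5), 78.1% v 81.8% (0.7) and 99.7% v 99.7% (0.9).

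**Chance imbalance.** The SD of the T0 difference between arms is sqrt(2/10) = 0.447 SD. The chance of a difference of at least 0.5 SD is 2 × [1 − Φ(0.5/0.447)] = 0.26. Given a T0 difference d, the raw-change contrast is shifted by (rho − 1)d. For d = 0.5 SD the size of the shift is 0.35 SD (rho 0.3), 0.25 SD (0.5), 0.15 SD (0.7) or 0.05 SD (0.9).

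**Validity over repeated randomisations.** With no true effect, simulated type I error at nominal 5% is 4.9% to 5.2% for raw change and 4.8% to 5.1% for the adjusted analysis. Neither is inflated.

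**The case against.** The strongest objection is that the article states no heart-rate analysis at all. A reader might infer that heart rate will be tested as raw change without T0. The document does not support that. Secondary Outcomes defines an outcome, not a model, and a change score can itself be adjusted for T0; in a linear model this gives exactly the same treatment effect as adjusting the follow-up value. Nor does the covariate list for secondary outcomes settle the matter, because the sentence goes on to name procedural length, which has no T0 value. The model may be in an analysis plan that is not shown. This objection stands, and it limits the point to what the text does: it fixes a change outcome and lists no T0 adjustment for it.

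A reader might also infer bias or false positives. That is not supported either. The shift from imbalance is conditional on the sample drawn; it averages to zero over randomisations, and type I error holds.

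A third inference would be that the heart-rate effect will set the size of the larger trial. The article already gives an expected 200 children and ties that number to no heart-rate figure.

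Finally, the gain depends on an unstated correlation, the power figures use normal-theory tests whereas the article plans nonparametric ones, and heart rate is a secondary outcome in a feasibility pilot that claims no power. All of this stands and keeps the point small. It does not remove it, because the stated outcome form can be improved with data already being collected.

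**Conclusion.** The point holds in a limited form. The article defines the physiological outcome as change from T0, intends a comparison between arms, collects T0, and lists no T0 adjustment. If the comparison is made without T0, it is valid but less precise at low to moderate correlation: raw change has about 45% more variance at rho 0.3, 26% at 0.5, 11% at 0.7 and 5% at 0.8, with no gain from adjusting at 0.9. There is about a one-in-four chance of a T0 difference of 0.5 SD or more, and at rho 0.5 such a difference moves the single estimate by 0.25 SD.

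These sizes rest on the assumed correlations, on equal spread at the two times, on normal data, and on T0 being unaffected by allocation. The importance is minor: a worthwhile clarification, not an error that threatens the trial's conclusions.

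**What to change.** In Secondary Outcomes and in Statistical Analysis, state that heart rate and saturation at T1 and T2 are compared between arms with the child's own T0 value as covariate. Rank-based analysis of covariance fits the nonparametric plan; ordinary analysis of covariance is an alternative for heart rate. Report the adjusted difference with its interval as the effect size, and keep raw change from T0 as a descriptive summary. If the analysis plan already adjusts the change for T0, one sentence in the protocol saying so is enough.

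The change is to wording only. T0 is already scheduled for measurement, no new data are needed, and the analysis spends one degree of freedom.

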#### Measures of Secondary Outcomes

The secondary outcomes will be measured as described here. Physiological parameters will be continuously measured using the Nellcor pulse oxygen saturation meter (Covidien), an approved and validated device. The occurrence of side effects will be collected from arrival on site to discharge from the study using a checklist of common side effects experienced while using VR and also related to dental medication. The length of the procedure will be measured and collected for every participant and will be compared with the average duration for a similar procedure that will have been measured prior to the study by the clinic’s personnel. Rescheduling of procedures in the event that cooperation is impossible will be noted. Salivary amylase levels, as a stress biomarker, will be measured before and after the dental procedure as described in the following section.

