#### Measurement of Salivary Amylase

Saliva samples will be collected from all children in this study at 2 different study time periods: before (T0) and after (T2) the intervention. Salivary alpha-amylase has been recognized and validated as a reliable and specific marker for autonomic nervous system activity and has been proposed as an alternative biomarker for stress [12]. Alpha-amylase sampling has been performed in previous studies to evaluate DFA for children undergoing dental procedures [28-30]. Alpha-amylase, as a salivary biomarker, can be considered an important and noninvasive tool for assessment of anxiety-related events, such as dental extraction and other treatment, for children [28,31].

Salivary samples will be collected using a sterile dental cotton swab from under the tongue 10 minutes before and 10 minutes after the procedure and stored immediately within a sterile vile in a research-specific on-site freezer. Samples will be collected by the dental resident and taken to the laboratory. Results will be entered in REDCap for analysis after the study.

Table 1 provides an overview of which questionnaires will be answered by which respondents during the study.

**Table 1 table1:** Questionnaires and corresponding respondents.

Questionnaires	Respondents
Parent or legal guardian satisfaction	Parents or legal guardians
Health care professional satisfaction	Health care professional
Anxiety score, physiological parameters	By proxy through research assistants

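### The only stated saliva comparison is a mean level at T2, with no stated use of the T0 sample taken from every child; adjusting amylase for T0 would be more precise

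*Protocol article*

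**What the plan says.** All references are to the protocol article.

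- **Secondary Outcomes.** Cardiac and oximetry measures are defined relative to baseline: "changes in physiological parameters (such as heart rate and pulse oximetry) during and after the intervention compared with baseline". The saliva marker in the same list is not: "rescheduling of procedures in the event cooperation is impossible, and (5) salivary amylase levels". No time point is attached to it.
- **Measures of Secondary Outcomes.** Two measurements are described: "Salivary amylase levels, as a stress biomarker, will be measured before and after the dental procedure".
- **Measurement of Salivary Amylase.** The paired sampling is universal: "Saliva samples will be collected from all children in this study at 2 different study time periods: before (T0) and after (T2) the intervention".
- **Statistical Analysis.** Amylase is not named. The one saliva analysis concerns "mean salivary cortisol level and mean difference in anxiety score", compared between the two groups at T2. The variables listed with it are procedure type, age, parental presence, the satisfaction levels and the T0 anxiety score. A T0 saliva value is not among them. The significance level is given "with a significance level (α) of .025, considering Bonferroni's correction".
- **Sample and Setting.** "All participants in this pilot study will be allocated in an equal ratio of 10 per group".

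**The concern.** Amylase is collected as a marker of stress around the procedure. A T2 level combines each child's resting value with the response to the procedure. The children are aged 6 to 17, have varied medical conditions and may have taken medication beforehand, so resting values may well differ between children. With 10 per arm, part of any T2 difference will reflect chance differences in resting level.

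The T0 sample is the obvious means of removing that part, and it is already planned. The analysis text nevertheless names a baseline for anxiety and none for saliva. Correcting cortisol to amylase would not change this, so the point is separate from the naming slip.

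What is at stake is the precision of the amylase effect estimate. The Statistical Analysis section says effect sizes will be assessed, and the Conclusion offers the results as preliminary data for a larger trial.

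**Working it through.** **The plan's own figures.** "This pilot will include 20 participants, totalling 10% of the expected 200 children to be included in the final study": 0.10 × 200 = 20, which reproduces. The significance level is 0.05 / 2 = 0.025, which reproduces if Bonferroni's correction is for two tests. The article gives no SD, T0–T2 correlation, effect size or power for amylase, so there is no amylase figure to reproduce.

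**Inputs.** n = 10 per arm (Sample and Setting). The T0–T2 correlation, rho, is assumed and shown over a range. Results are in units of the between-child SD, taken as equal at T0 and T2. They use a normal approximation. The plan intends nonparametric tests, so the figures indicate relative precision only.

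**Chance baseline imbalance.**
- SD of the difference in mean T0 between arms = sqrt(2/10) = 0.447.
- P(|difference| > 0.5 SD) = 2 × [1 − Φ(0.5 / 0.447)] = 2 × [1 − Φ(1.118)] = 0.264.
- An imbalance of 0.5 SD at T0 shifts the expected T2 difference by rho × 0.5 SD, that is 0.15 SD at rho 0.3 and 0.40 SD at rho 0.8. It does not carry over in full.

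**Three ways to compare the arms.** SE of the arm difference:
- T2 only: sqrt(2/10) = 0.447, whatever rho is.
- Raw change: 0.447 × sqrt(2(1 − rho)).
- T2 adjusted for T0: 0.447 × sqrt(1 − rho²).

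Estimating one extra covariate with 20 children costs a factor of about 1 + 1/16, or about 6% of variance. The fourth column below includes it. The last column is 10 / (1 − rho²), before that loss.

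| rho (assumed) | SE, raw change | SE, adjusted | Variance left by adjustment: before / after the 1/16 loss | T2-only trial of equal precision, per arm |
|---|---|---|---|---|
| 0.3 | 0.529 | 0.427 | 91% / 97% | 11.0 |
| 0.5 | 0.447 | 0.387 | 75% / 80% | 13.3 |
| 0.7 | 0.346 | 0.319 | 51% / 54% | 19.6 |
| 0.8 | 0.283 | 0.268 | 36% / 38% | 27.8 |

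At rho 0.3 almost nothing is gained. At 0.7 or above, the variance is roughly halved or better. The raw change score is less precise than T2 alone when rho is below 0.5 (0.529 against 0.447 at 0.3). It is less precise than the adjusted comparison at every value shown.

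**Timing of T0.** Measurement of Salivary Amylase places the first swab 10 minutes before the procedure. Study Proceedings has the resident obtain and announce the allocation 10 minutes before the intervention starts. The order of the two is not stated.

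**The case against.** The best defence has three parts.

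1. **Silence is not exclusion.** No section says the T0 sample will be left out, several describe measurement before and after, and a separate data analysis plan is mentioned but not shown. A reader might infer that the plan discards T0; the article does not support that. It does go further than silence, however. It states a statistic (a mean level), a time point and a list of variables, and that list contains a baseline for anxiety but none for saliva. The supportable statement is that the between-group comparison makes no stated use of T0.

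2. **The sentence is faulty.** It names cortisol, so its word *level* is weak evidence of a deliberate choice, and reading it as amylase is an inference. The contrast with anxiety is also uncertain, because the mean difference in anxiety score may be a difference between groups and not a change from baseline. This stands as a caution. The inference remains the most plausible reading, since no other section mentions cortisol.

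3. **Randomisation protects the comparison.** A reader might infer that a T2-only comparison is biased, or that differences between children overwhelm the stress response. Neither follows. The comparison is unbiased on average, and its standard error already allows for chance imbalance. With no SD, correlation or effect for amylase in the article, nothing shows that the response would be overwhelmed. What survives is a loss of precision whose size depends on an unknown correlation.

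**Conclusion.** The point holds as one of precision and clear definition. The article states a T2 level comparison for saliva and no role for a baseline sample that every child gives. Adjusting for T0 is a concrete improvement on that.

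The 26% imbalance figure depends only on 10 per arm and approximate normality of the arm means. The size of the gain depends on the assumed correlation and runs from negligible at 0.3 to substantial at 0.7 or 0.8. The conclusion also rests on reading cortisol as amylase. It concerns a secondary outcome in a pilot whose main purpose is feasibility and acceptability, so the priority is modest.

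**What to change.** In Secondary Outcomes and Statistical Analysis, name salivary alpha-amylase and state that T2 is compared between arms adjusted for T0, by one method chosen in advance:

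- ANCOVA on log amylase, with the effect reported as an adjusted ratio between arms; or
- rank-based ANCOVA, which keeps the nonparametric approach, with a rank-based effect size. This does not estimate a ratio, so the two options should not be mixed.

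Do not rely on a raw change score.

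In Study Proceedings, state that the T0 swab is taken before the allocation is announced. Otherwise knowledge of the arm could already affect the baseline value.

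Both samples are already planned, so no extra data are needed. The cost is a few sentences and one degree of freedom, about 6% of variance at n = 20. The loss would be somewhat larger if procedure type, age and parental presence enter the same model. At a correlation near 0.3 that cost takes up most of the gain.
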